## Abstract

**Background:**

Multiple sclerosis (MS) is an inflammatory and degenerative disease of the central nervous system. More than 90,000 Canadians are affected; a cure is yet to be found. Available treatments to manage the disease course are only partially effective. For many years, persons with MS (PwMS) have used cannabis to relax, to reduce pain and spasticity, or to improve sleep and daily functioning, despite the lack of scientific evidence on the efficacy of specific cannabinoids [i.e., tetrahydrocannabinol (THC) and cannabidiol (CBD)] on these MS symptoms. The purpose of this clinical trial is to assess the effectiveness of different doses of these cannabinoids, alone or combined, on spasticity relief, compared to placebo. Moreover, we aim to determine which treatment is best effective to address other key MS conditions.

**Methods:**

A double-blinded, randomized, factorial, placebo-controlled trial will be performed. We intend to include up to 250 PwMS aged over 21 recruited from the Centre hospitalier de l’Université de Montréal MS Clinic. PwMS will be randomly assigned on a 1:1:1:1 ratio to one of the trial arms: THC alone, CBD alone, THC/CBD combination, or placebo, using stratified blocked randomization, with random blocks within each stratum. The primary outcome is a self-assessment of spasticity using the mean Numeric Rating Scale score over 7 days. The main outcome will be the difference in this score at 4 weeks compared to baseline. Secondary outcomes include assessments of spasticity as measured by a clinician, pain, fatigue, sleep, bowel, bladder, and sexual dysfunction, restless legs syndrome, mental health, quality of life, mobility, cognitive functioning, and adverse events. Treatment responders are eligible for a 12-week extension phase, using the same treatment allocation and assessments.

**Discussion:**

Previous clinical studies examined the efficacy of cannabis-based medicines in PwMS, mostly using products with 1:1 THC/CBD ratio. The major barrier to effectively use cannabis in real-world clinical settings is the lack of evidence on benefits of specific cannabinoids and information on possible related risks. The CANSEP study will contribute to overcome these limitations and identify the risks and benefits of cannabis-based treatments in PwMS.

**Clinical trial registration:**

ClinicalTrials.Gov, NCT05092191.

## Introduction

1

Multiple sclerosis (MS) is an inflammatory disease of the brain and spinal cord afflicting over 90,000 Canadians (1). MS causes numerous symptoms, such as spasticity, pain, sphincter and sleep dysfunction, fatigue and depression (2). Spasticity has been reported in up to 80% of persons with MS (PwMS) (3). It is described as an involuntary increase in muscle tone, tightness, and spasms of the affected limbs. It is part of the upper motor neuron syndrome, which also comprises weakness, increased deep tendon reflexes, and the Babinski sign (4, 5).

Despite the growing number of available disease-modifying treatments, none are curative (6, 7). PwMS still carry a heavy burden of undermanaged symptoms (8). Current spasticity therapeutic approaches include muscle relaxants such as baclofen, tizanidine, and clonazepam. Injections of botulinum toxin are used for focal spasticity (9, 10). They are effective but must be repeated every 3 to 4 months. Diffuse and extreme spasticity responds well to intrathecal injections of baclofen delivered through an intra-abdominal programmed pump reservoir (11).

Cannabinoids have also been proposed as a potentially useful addition to current therapies to treat MS symptoms. Studies conducted in the United States, where cannabis is legal in most states, have reported that 35 to 40% of PwMS use cannabis (12, 13). Both prescribed and non-therapeutic cannabis products are legally accessible since 2018 to all adults in Canada (14). Sixty-five percent of Canadian PwMS have already been using cannabis to ameliorate mood, improve sleep, and/or relieve pain and spasticity (15). Analgesic, antihyperalgesic, neuro-protective, and anti-inflammatory properties have been attributed to tetrahydrocannabinol (THC) and cannabidiol (CBD) (16). A systematic review concluded that oromucosal nabiximols (~1:1 THC:CBD ratio) are safe and efficient to treat MS spasticity (17–19).

Unfortunately, whether specific cannabis derivatives (CBD vs. THC) or other forms can be specifically optimized to manage MS symptoms remains largely unexplored. A variety of cannabinoid-based products are now available and widely used by PwMS, as mentioned previously, despite the lack of robust scientific evidence to guide their decision. Few studies have systematically compared the two main cannabinoids (THC and CBD) individually or combined for the treatment of spasticity (20), but no Canadian trial has previously compared the cannabinoids. Furthermore, the potential mechanisms mediating the therapeutic and/or adverse events (AEs) (e.g., gastrointestinal and central nervous system such as psychopathologic/cognitive AEs) of cannabis-based medicines in PwMS are poorly documented (20).

In response to this gap in knowledge, this trial will document medical cannabis (THC, CBD, and their combination) as a novel treatment with the potential to improve spasticity and other MS symptoms and produce evidence-based knowledge to guide its use.

### Hypothesis

1.1

We hypothesize that the administration of different doses of THC alone, CBD alone, and THC and CBD combined will result in a significant relief of spasticity compared to placebo.

### Study objectives

1.2

The main aims of this study are: (1) to compare the efficacy of THC and CBD, alone and in combination, as add-on therapies to the current standard treatments for relief of spasticity in PwMS, (2) to assess the tolerability profile of THC and CBD, alone and in combination, (3) to identify the mechanisms underlying such therapeutic and adverse effects, considering sex, age, pharmacology, and immune profile.

## Methods/design

2

### Study overview

2.1

CANSEP is the first Canadian randomized clinical trial focusing on interventions with THC, CBD, or their combination, for the treatment of spasticity in PwMS. Our study is part of the Integrated Cannabis Research Strategy funded by the Canadian Institutes of Health Research (21), and MS Canada. The overarching vision of the Integrated Cannabis Research Strategy is to catalyze future research related to the health impacts of cannabis legalization, to validate the potential therapeutic benefits of cannabis, to understand risks and harms, and to support policy and regulatory models for studying cannabis use. Thus, CANSEP will explore in depth the potential therapeutic benefits and harms associated with cannabis use to strengthen the evidence base and to build cannabis-related research capacity in the field of MS. The study duration is 5 years as summarized in the schedule presented in the Supplementary material. Recruitment has begun on November 10, 2022. As of May 29, 2024, 50 participants have been enrolled, and of these, 41 have been randomized.

### Study design

2.2

CANSEP is a double-blinded, randomized, factorial, placebo-controlled trial in a cohort of PwMS with an incomplete response to standard treatments, using various measurements, and thorough, multidisciplinary outcomes. Up to 4 visits are scheduled during this trial. Visit 1 is dedicated to the consent process and the confirmation of eligibility criteria. Outcomes assessments are done during visit 2 (baseline) and during visit 3 which takes place after 4 weeks of treatment. Finally, outcomes assessments are also carried out during a fourth visit which is scheduled 12 weeks after the end of the initial treatment period for responders only, i.e., patients who have a decrease in mean Numeric Rating Scale (NRS) of at least one point compared to baseline. Indeed, spasticity will be assessed using the NRS (22), but the spasticity outcome analyzed in this trial will be the mean NRS score over 7 days (mNRS). Blood samples will be collected to measure immunological and neurobiological markers in order to investigate the underlying physiological responses of each treatment administration, and to identify potential mechanisms of their therapeutic effects. The study plan is represented in Figure 1.

**Figure 1 fig1:**
[figure not shown]
Overview of the CANSEP study design. Only treatment responders are eligible to the extension phase (i.e., those with an improvement of at least one point on the mNRS). Blood samples will be collected at baseline and after the treatment period, while primary, secondary, and exploratory outcomes will be assessed starting from the baseline visit. Different treatment bottles are used for illustrative purposes only. PwMS, persons with multiple sclerosis; mNRS, mean score of the Numeric Rating Scale over 7 days; CBD, cannabidiol; THC, tetrahydrocannabinol; BID, twice a day. Created with BioRender.com.

### Study population

2.3

The CANSEP study seeks to identify a cohort of PwMS according to the 2017 revised McDonald criteria (23), from the Centre hospitalier de l’Université de Montréal (CHUM) MS Clinic. Our study sample will be representative of the sex distribution of MS, which is 2.6 higher in women than in men in Canada (1). It will recruit adults of at least 21 years of age [the legal age in the province of Quebec to use cannabis products (24)], who reported a mean level of spasticity over 7 days of 2 points or more on the mNRS. All potential participants will be screened to determine their eligibility according to the following inclusion and exclusion criteria:

Inclusion criteria: (a) Be diagnosed with MS (any subtype), for at least six months, by a MS neurologist, according to the 2017 revised McDonald criteria (23); (b) Spasticity or symptoms related to spasticity due to MS of at least one-month duration and not relieved with current therapy, at a mean level of 2 or more on the mNRS; (c) Have a stable dose of standard therapies for at least 4 weeks prior to the screening visit and willingness to maintain such therapies for the duration of the study; (d) Aged 21 years or older (24); (e) Have the ability, in the investigator’s opinion, and willingness to comply with all study requirements; (f) Able to speak and read French or English (grade nine level of language required).Exclusion criteria: (a) Concomitant disease with symptoms of spasticity, or that may have influenced their level of spasticity; (b) Received a botulinum toxin injection within four months prior to the screening visit or unwillingness to stop receiving botulinum toxin injections for the duration of the study; (c) Use of cannabis or cannabinoid-based products within 7 days prior to study entry and unwillingness to abstain from use of cannabinoids for the duration of the study; (d) History of schizophrenia, other psychotic illness, or other significant psychiatric disorder other than anxiety or depression associated with their underlying condition; (e) Alcohol or substance abuse disorder other than nicotine; (f) History of epilepsy or recurrent seizures; (g) Hypersensitivity to cannabinoids or any of the excipients of the study medication; (h) Clinically relevant cardiac dysfunction within the last 12 months or had a cardiac disorder that, in the opinion of the investigator, would put the subject at risk of a clinically relevant arrhythmia or myocardial infarction; (i) Impaired renal function, i.e., serum creatinine clearance lower than 50 mL/min; (j) Significantly impaired hepatic function, at visit 1, in the investigator’s opinion and/or had liver function tests of equal to or greater than three times the upper limit of normal; (k) Pregnancy or breastfeeding; (l) Men with history of fertility problems and who plan to conceive at any time in the future; (m) Any participant who plans to conceive either at screening or while enrolled in the study; (n) Inability (or unwillingness) of women of childbearing potential and men to use a medically acceptable form of contraception throughout the study duration; (o) Any other significant disease or disorder which, in the opinion of the investigator, may either put the subject at risk because of participation in the study, may influence the result of the study, or the subject’s ability to participate in the study; (p) Intention to travel internationally, or to donate blood during the study.

### Randomization

2.4

Patients who meet all the inclusion criteria and none of the exclusion criteria and consent to take part in the trial after they have received the study oral and written information, will then be randomly assigned in equal proportions to either THC, CBD, THC + CBD, or placebo using stratified block randomization. Randomization will be stratified by sex and baseline mean spasticity score. In each of the 4 strata, corresponding to different combinations of sex (male vs. female) and baseline mean spasticity score ([2-6[vs. ≥6), randomization will be performed using blocks of size 4. This will minimize the imbalance between group sizes, while preventing unblinding of the treatment allocation of consecutive participants. The randomization schedule will be generated by CHUM’s Centre for the Integration and Analysis of Medical Data (CITADEL), who will send the randomization codes to the CHUM research pharmacy and keep secure digitalized copies. Randomization codes will be maintained throughout the study.

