#### Arms and intervention

2.5.1

An authorization to conduct the CANSEP trial using THC and CBD manufactured by PurCann Pharma was obtained from Health Canada prior to the start of recruitment.

Participants will be allocated to four arms and initially receive THC (4 mg/day), CBD (40 mg/day), THC/CBD combination (THC 4 mg/day and CBD 40 mg/day), or placebo, on the first day. Every two days, the daily quantity will be multiplied by two up to a maximum of 20 mg for THC and 200 mg for CBD, if well tolerated (Table 1). The selection of doses is based on previous studies on cannabinoids in MS (19, 25–34), and on a systematic review indicating that a daily dose of 200 mg of CBD is effective for other neurological conditions and symptoms while being well tolerated (35). One of the authors’ expert opinion on cannabinoids in psychiatric research and clinical practice (36, 37), and the approved and available orally formulated cannabinoids in Canada (38, 39) also accounted for these doses’ selection. THC and CBD will be taken as softgels (cannabis extract; placebo will taste and look exactly the same), in two divided doses per day at 12-h intervals. Participants will receive the allocated treatment for a total of 4 consecutive weeks, followed by an additional 12 weeks of treatment for responders who will be identified as those who have a decrease from baseline in spasticity of at least one point on the mNRS. Participants enrolled in the trial will continue stable doses of other standard treatments for spasticity including muscle relaxants (baclofen, tizanidine, and clonazepam) (18).

**Table 1 tab1:** Medication dosage.

Treatment period (4 weeks)					
Week	Day	Daily THC dose (mg)^a^	Daily CBD dose (mg)^a^	Daily THC and CBD combined dose (mg)^a^	
				THC	CBD
W1	#1	4	40	4	40
	#2	4	40	4	40
	#3	8	80	8	80
	#4	8	80	8	80
	#5	16	160	16	160
	#6	16	160	16	160
	#7	20	200	20	200
W2 to W4 included		20	200	20	200
Extension period (12 weeks)					
Week		Daily THC dose (mg)^a^	Daily CBD dose (mg)^a^	Daily THC and CBD combined dose (mg)^a^	
				THC	CBD
W5 to W16 included		20	200	20	200

^a^Treatment will be taken in two divided doses per day at 12-h intervals. CBD, cannabidiol; THC, tetrahydrocannabinol; W, week.

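### Section 2.4 credits a single published block size of 4, the smallest possible for four arms, with preventing unblinding, a protection it does not give; the abstract's block wording is ambiguous

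*Protocol article*

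**What the plan says.** The abstract gives four arms in equal ratio ("PwMS will be randomly assigned on a 1:1:1:1 ratio to one of the trial arms"), allocated "using stratified blocked randomization, with random blocks within each stratum".

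Section 2.4 (Randomization) is more specific. "Randomization will be stratified by sex and baseline mean spasticity score", which gives four strata: sex crossed with a baseline score below 6 or at least 6. In each stratum, "randomization will be performed using blocks of size 4". The section then justifies this choice: it limits imbalance in group sizes "while preventing unblinding of the treatment allocation of consecutive participants". The hospital's data centre generates the schedule and sends the codes to the research pharmacy.

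On masking, section 2.2 states that "CANSEP is a double-blinded, randomized, factorial, placebo-controlled trial", and section 2.5.1 says of the softgels that "placebo will taste and look exactly the same". Section 2.6.3 plans a blinding index for participants after the initial treatment period, and its Table 2 lists the euphoric and paranoid-dysphoric effects of cannabis as an outcome. Section 2.1 reports 41 participants randomized by May 29, 2024, with recruitment still open.

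**The concern.** A permuted block must be a multiple of the number of arms, so 4 is the smallest size available here, and it is the only size stated. It is also now published while participants are still being randomized. The stated rationale runs two properties together. A small fixed block does keep group sizes close. It does not protect against prediction, because it makes the end of a block the easiest part of the list to work out once the start of that block is known.

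This matters because matching softgels hide appearance and taste but not pharmacological effects. All participants come from one clinic (section 2.3), so the same team may see consecutive participants in a stratum. Several eligibility criteria in section 2.3 rest on the investigator's opinion (inclusion e; exclusions h, j and o). That leaves room for selective enrolment if the next allocation is predictable.

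**Working it through.** The article states no figure on this point, so there is none to reproduce. The check is an enumeration.

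**Inputs.** Four arms, 1:1:1:1 (abstract); block size 4 in each of 4 strata (section 2.4). Two of the four arms contain THC and two do not. Assumption: the guesser knows the block size and can count where each block starts in a stratum.

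**1. Blind intact, no earlier arm known.** All 4! = 24 orders are equally likely, so each arm has probability 1/4 at every position. Nothing can be deduced.

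**2. All earlier arms in the block known.** The chance of guessing the next arm is 1/4, 1/3, 1/2 and 1 at positions 1 to 4.
- Mean: (0.250 + 0.333 + 0.500 + 1.000)/4 = 2.083/4 = 52%, against 25% under simple randomization.
- Certain allocations: 1 of 4 = 25%.

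**3. Only THC yes/no recognised, perfectly.** Each block is one of 6 orders of two THC and two non-THC places. The remainder is determined once both places of one kind are used, so the determined part is the final run.
- Determined: (2+2+1+1+1+1)/6 = 1.33 of 4 = 33%.
- Correct guesses: (1/2 + 2/3 + 2/3 + 1)/4 = 2.833/4 = 71%, against 50% by chance.

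**4. Imperfect recognition.** The documents give no recognition rate. Suppose (assumption) that each earlier participant is correctly recognised with probability r, independently, and is otherwise left unclassified.
- THC yes/no: position 3 is determined if the first two are of the same kind (probability 1/3) and both are recognised (r²). Position 4 is determined if the two of the same kind among the first three are both recognised (r²). Share = (r²/3 + r²)/4 = r²/3.
- Exact arm: position 4 is certain only if all three are recognised. Share = r³/4.

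| r | THC status determined | Exact arm certain |
|---|---|---|
| 0 | 0% | 0% |
| 0.25 | 2% | 0.4% |
| 0.50 | 8% | 3% |
| 0.75 | 19% | 11% |
| 1 | 33% | 25% |

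**5. Is there time to observe earlier participants?** From November 10, 2022 to May 29, 2024 is 566 days; 566/41 = 13.8 days per randomization across all strata, or 13.8 × 4 = about 55 days per stratum if the strata fill equally (assumption). Table 1 reaches full dose on day 7. On average, then, a participant would have reached full dose before the next in the same stratum is randomized. The gap is a little shorter if the first randomization came after recruitment opened.

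**6. Effect of varying sizes.** Sizes 4 and 8, equally likely (assumption), were simulated over 15,000 blocks. The guesser knows the possible sizes but not the realized ones and updates by Bayes' rule.

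| Earlier knowledge | Measure | Fixed 4 | Random 4/8 |
|---|---|---|---|
| Arms | Certain | 25% | about 8% |
| Arms | Guessed correctly | 52% | about 49% |
| THC yes/no | Certain | 33% | about 8% |
| THC yes/no | Guessed correctly | 71% | about 68% |

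**The case against.** Three stronger readings are tempting, and the document supports none of them fully.

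**That the abstract and section 2.4 contradict each other.** The abstract does not say random sizes. Its phrase also fits blocks of fixed size in random order, which agrees with section 2.4. What stands is ambiguity: a reader cannot tell which scheme is in use.

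**That allocations can be deduced as the plan stands, so the blind fails.** The placebo is matched, and the article names only the data centre and the pharmacy as handling the codes. Block size alone reveals nothing (step 1). A small block amplifies a breach but does not create one. That cannabis effects are recorded as an outcome does not show that staff can identify them reliably, so the 25% and 33% figures are upper limits. What stands is that the article itself treats the success of blinding as something to be tested. The planned index covers participants, not predictability for staff.

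**That the self-rated primary outcome is thereby biased.** Deduction from blocks would inform staff, not participants. A participant who guesses the arm from THC effects does so at any block size. Staff expectations could be passed on, but the more direct route to harm is selective enrolment.

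It is also fair to say that varying sizes barely reduce average guessing. Their gain lies in certainty, which is what most enables selective enrolment.

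**Conclusion.** The point holds in a limited form. Section 2.4 states one fixed block size equal to the number of arms and claims a protection that this size does not provide, and the abstract's description needs reconciling with it. The consequence is a conditional risk and not a demonstrated loss of blinding: zero if no earlier allocation is known, rising to 25% of allocations certain by arm, or 33% determined by THC status, if every earlier allocation in the block is recognised without error. The result rests on knowledge of block size and block start, and on a recognition rate that the document does not give. The change should be made because it is cheap and recruitment was far from complete at the stated date: (250 − 41)/250 = 84% of the larger target remained, or (200 − 41)/200 = 80% of the 200 also mentioned in section 2.7.1. It does not put the primary analysis in question.

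**What to change.** - For the unused part of the schedule, have the data centre generate permuted blocks of randomly varying size (for example 4 and 8) within each of the four strata, and send the new list to the research pharmacy only.
- Do not disclose the sizes to site staff or publish them before recruitment closes.
- Correct the rationale in section 2.4: blocking limits imbalance, while unpredictability comes from varying, undisclosed sizes together with masking. Align the abstract with it.
- If varying sizes are already in use, no new list is needed; correct section 2.4 only and remove the fixed size.

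The cost is one new list and a text correction. The downside is slightly larger possible imbalance. An unfinished block of 4 leaves two arms differing by at most 1 in a stratum, and a block of 8 by at most 2, so across four strata the worst case goes from 4 to 8 participants. The planned covariate analysis in section 2.7.2 already adjusts for baseline score and sex, so this should matter little.
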